### Statistical analysis

Analyses will be performed according to the intention-to-treat principle. Patients who are lost or die before completing the 3-month follow-up visit will be excluded from the analysis of the primary endpoint. The proportions of patients with recurrence at follow-up in the dapagliflozin group and the placebo group will be compared using the chi-square test. In general, the last date of contact for each patient will be considered the censoring date for those without any primary outcome event. The cumulative incidence of the first occurrence of any event in the primary endpoint will be plotted by the Kaplan–Meier curve. In addition, the logistic regression model will be used to assess possible predictors for recurrence at follow-up, and pre-specified relevant clinical characteristics will be tested first in a univariate and then in a multivariate-adjusted model.

Continuous variables will be expressed as the mean ± standard deviation or the median and the interquartile range, and Student’s *t*-test, the Mann–Whitney test, and the Wilcoxon rank sum test will be used for comparisons where appropriate. The chi-square test will be performed to analyse categorical variables, which are expressed as frequencies and proportions, and Fisher’s exact test will be used as appropriate. All tests will be two sided, and *P* < 0.05 will be considered to indicate statistical significance. Statistical analyses will be performed by SPSS software (version 26.0).

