### Outcome measurement

Primary endpoint is any documented atrial tachyarrhythmia [AF, atrial flutter or atrial tachycardia (AF/AT)] lasting 30 s following a blanking period of 3 months after CMIV.

Secondary endpoints are as follows: (i) any documented atrial tachyarrhythmia [AF, (AF/AT)] at the 6-month follow-up monitoring session after CMIV; (ii) any documented atrial tachyarrhythmia [AF, (AF/AT)] at the 12-month follow-up monitoring after CMIV; and (iii) major adverse cardiac or cerebrovascular events (MACCEs, including cardiovascular death, malignant arrhythmias, and stroke) at 6 or 12 months after CMIV.

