### Data collection

Study visits are scheduled to occur before randomization and at 3, 6, and 12 months; a detailed medical history, a routine blood pressure measurement and physical examination, laboratory testing, and 48- to 72-h Holter monitoring will be conducted at each visit. All patients with arrhythmia-related symptoms, especially after the blanking period, will be encouraged to undergo electrocardiography (ECG) during their symptomatic periods, and such events will be registered with the study investigator. In addition, patients who experience longer-lasting arrhythmia symptoms will be instructed to contact local hospitals and undergo cardioversion within 48 h, and additional monitoring (e.g. extra Holter or event monitoring) will be performed for patients with arrhythmia symptoms who cannot be monitored during an acute episode. All ECGs and Holter monitoring will be reviewed by a blinded study investigator. Peri-operative clinical and baseline data, such as the type of AF, medical history, laboratory results, complications, cardiac ultrasound features, general information about the operation, a record of surgical ablation, post-operative complications, and pre-operative medication, will be collected through the electronic medical record database.

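### The primary endpoint and its chi-square test name no end month, and the test cannot use the plan's own last-contact censoring rule

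*Protocol article*

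**What the plan says.** All references are to the Protocol article.

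- **Endpoint.** Outcome measurement defines the primary endpoint as a documented atrial tachyarrhythmia "lasting 30 s following a blanking period of 3 months after CMIV". The Abstract gives the same definition. It has a start and no end.
- **Secondary endpoints.** The same arrhythmia is assessed "at the 6-month follow-up monitoring session after CMIV" and "at the 12-month follow-up monitoring after CMIV". These are the only rhythm endpoints with a month attached.
- **Visits.** Data collection states: "Study visits are scheduled to occur before randomization and at 3, 6, and 12 months". Holter monitoring of 48 to 72 hours is done at each visit.
- **Test.** Statistical analysis: "The proportions of patients with recurrence at follow-up in the dapagliflozin group and the placebo group will be compared using the chi-square test". No month is named.
- **Exclusion.** "Patients who are lost or die before completing the 3-month follow-up visit will be excluded from the analysis of the primary endpoint".
- **Censoring.** "the last date of contact for each patient will be considered the censoring date for those without any primary outcome event".
- **Use of event times.** "The cumulative incidence of the first occurrence of any event in the primary endpoint will be plotted by the Kaplan–Meier curve". No test that accounts for censoring is named.
- **Interim.** Adverse events monitoring and interim analysis places the interim look at 75% of confirmed primary events. The final significance level depends on the event count and on the timing of that look.

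**The concern.** A comparison of two proportions needs one window that is the same for every patient, and a rule for patients who do not complete it. The article supplies neither for the confirmatory test. It does supply a censoring rule, but that rule fits a time-to-event comparison, which is not the one chosen.

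Three things are at stake.

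- **The estimand.** Recurrence from month 3 to month 6 and recurrence from month 3 to month 12 are different quantities. With the end open, the window could be settled after data are seen.
- **Late losses.** Only losses and deaths before the 3-month visit leave the analysis. A two-by-two table over everyone else has no cell for a patient who was event-free when last seen at, say, month 7, except the recurrence-free cell.
- **The interim.** Recruitment is expected to run from 1 September 2023 to late June 2024, about ten months. When an event count triggers the look, late recruits will have been observed for less time than early ones, and raw proportions then mix recurrence with observation time.

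A smaller gap is that the 3-month Holter falls on the edge of the blanking period, and the text does not say whether an episode on it counts.

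**Working it through.** **Inputs from Sample size estimation.** Recurrence-free proportions 0.821 (dapagliflozin) and 0.621 (placebo), so recurrence 0.179 and 0.379; two-sided alpha 0.05; power 0.90; unpooled Z-test; 10% dropout; 120 enrolled per group, hence 120 × 0.9 = 108 evaluable. The article gives no time point for the 37.9% and no rate of loss after month 3.

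**1. The plan's own figure.** n = (1.960 + 1.2816)² × (0.821×0.179 + 0.621×0.379) / 0.200² = 100.4, rounded up to 101 per group. This matches the article.

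**2. Effect of the horizon.** *Assumption:* constant hazard from month 3, with the planning rates holding at month 12. Month 6 is then 3 of 9 months at risk.

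- Placebo: 1 − 0.621^(1/3) = 0.147
- Dapagliflozin: 1 − 0.821^(1/3) = 0.064

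Power = Φ(difference / √[(p₁q₁ + p₂q₂)/n] − 1.960):

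| Horizon | Rates | Power, 108 per group | Power, 120 per group |
|---|---|---|---|
| Month 12 | 37.9% vs 17.9% | 91.9% | 94.3% |
| Month 6 | 14.7% vs 6.4% | 52.1% | 56.4% |

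**3. Equal loss after month 3, lost patients counted as recurrence-free.** *Assumption:* exponential loss reaching a fraction L by month 12. With H = −ln(1 − p) and C = −ln(1 − L), the observed proportion is H/(H + C) × [1 − (1 − p)(1 − L)].

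At L = 10%:

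- Placebo: 0.4764/0.5818 × (1 − 0.621×0.9) = 0.361
- Dapagliflozin: 0.1972/0.3026 × (1 − 0.821×0.9) = 0.170

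The difference is 19.1 points instead of 20.0. A cruder calculation that places all losses midway gives 0.360 − 0.170 = 19.0 points. At L = 20% the difference is 18.2 points. Power at 120 per group goes from 94.3% to 92.9% (10% loss) and 91.2% (20% loss).

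**4. Unequal loss with no drug effect.** Both arms have a true rate of 37.9%, with 120 per group. For 5% lost on placebo and 15% on dapagliflozin, the observed proportions are 0.370 and 0.352, a spurious difference of 1.8 points. The standard error is √(2 × 0.361 × 0.639 / 120) = 0.062, so the shift is 0.0181/0.062 = 0.29. Type I error = Φ(−1.96 − 0.29) + Φ(−1.96 + 0.29) = 6.0%.

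| Loss, placebo vs dapagliflozin | Observed recurrence | Two-sided type I error |
|---|---|---|
| 5% vs 15% | 37.0% vs 35.2% | 6.0% |
| 0% vs 20% | 37.9% vs 34.3% | 9.0% |
| 10% vs 30% | 36.1% vs 32.3% | 9.5% |

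**5. What a log-rank test would need.** HR = ln 0.821 / ln 0.621 = 0.414.

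- Schoenfeld: 4 × (1.960 + 1.2816)² / (ln 0.414)² = 54.0, i.e. 54 to 55 events.
- Freedman: (1.960 + 1.2816)² × [(1 + 0.414)/(1 − 0.414)]² = 61.2, i.e. 62 events.
- Expected at 108 per group: 108 × (0.379 + 0.179) = 60.3.

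With 60.3 events, power is Φ(√60.3 × 0.882/2 − 1.960) ≈ 93% by Schoenfeld and Φ(√60.3 × 0.414 − 1.960) ≈ 90% by Freedman.

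**The case against.** Much can be said for the plan as it stands.

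- **The chi-square matches the sample size.** The trial was sized for that test and the figure reproduces. The censoring sentence directly precedes the Kaplan–Meier sentence and can be read as serving the curve alone. Scheduled rhythm monitoring after blanking is only at months 6 and 12, so many event times will be visit-driven, and a binary comparison at a fixed month would be legitimate. This stands: a chi-square is not wrong in itself. It needs a fixed month and a rule for late losses, and the article gives neither.
- **Late losses are not said to be recurrence-free.** Correct. A reader might infer that the plan states this; it does not. It follows from the exclusion rule together with a test that has no place for censoring. A full protocol or analysis plan might say more.
- **Unequal loss is unlikely.** The trial is double-blind with matched placebo, treatment ends at month 3 in both arms, and consenting patients with a telephone are called monthly. Nothing in the text points to differential loss, so step 4 is illustrative. The calls ask about cardiovascular and serious adverse events and do not replace a Holter.
- **Month 12 is the natural reading.** It is the last visit, and month 6 is explicitly secondary. A reader might infer that the trial has only 52% power. The documents do not support that: the figure needs the less likely reading, a constant hazard, and 37.9% being a month-12 rate.
- **The flowchart is not shown** and could place the endpoint on a timeline. That limits certainty about the whole document set but does not close the gap in the text.

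**Conclusion.** The point holds in a limited form. The primary endpoint and its test have no stated end month, and the confirmatory comparison cannot use the censoring rule set out beside it. The censored data feed only a plot.

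The open horizon is the more serious part, because the planning rates, and hence the power, apply at one time point that is never named. The month-6 power figure shows how much depends on that choice; it is not an estimate of the trial's actual power.

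The bias from late loss is secondary: about one point of the 20-point difference if 10% are lost in each arm, and more than nominal type I error only if loss differs by arm. Both results assume a constant hazard, exponential loss and loss rates that the article does not give. The sizing arithmetic is sound given its inputs and is not part of this point.

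**What to change.** 1. **Name one horizon** for the primary endpoint, for example from the end of the blanking period to the 12-month visit, and state the month to which 37.9% and 17.9% refer.
2. **State whether an episode on the 3-month Holter counts** when the recording falls on the blanking boundary.
3. **Align the primary comparison with the censoring rule:** a log-rank test, or the Kaplan–Meier risk difference at 12 months with its 95% confidence interval. Use the same method at the interim, where follow-up is unequal. Keep the chi-square as supportive.

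If the binary test is kept as primary, the minimum is a fixed month and a written rule for patients lost after month 3.

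**Cost.** No new data are needed. The change is not confined to the analysis section: Sample size estimation rests on the chi-square and must be restated in events. With 54 to 62 events needed and about 60 expected at 108 per group, power is roughly 90%, with little to spare on the Freedman count. Because many event times will be set by the 6- and 12-month visits, the log-rank test gains little timing information; its benefit is that it handles incomplete follow-up.

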### Adverse events monitoring and interim analysis

Adverse events will be constantly monitored by investigators during the process of the study through regular medical check-ups, and the details will be immediately reported to the principal investigator once an AE occurs, regardless of the causal relationship with dapagliflozin. Only serious AEs and AEs of interest or those leading to premature study drug discontinuation, study drug interruption, or dose reduction are recorded. Adverse events of interest include volume depletion, renal events, major hypoglycaemia, and potential diabetic ketoacidosis.

The collection of cardiovascular events and other serious AEs will be performed by two well-trained staff members, and they will follow up specifically for these events by telephone every month for every participant with a phone number who has given prior consent during enrolment. In addition, participants will also be taught and asked to report whether they have experienced any cardiovascular events or other serious AEs. All captive cardiovascular events and other serious AEs will be adjudicated and graded by two well-trained staff members in order to reach a consensus.

Once 75% of the primary events are confirmed, an interim analysis will be performed by using a Haybittle–Peto rule, and if the superiority of dapagliflozin over placebo is demonstrated for the primary outcome with a sided level of 0.001, early termination of the trial can be recommended. The significance level of the final analysis will be determined by the Haybittle–Peto rule, depending on the actual number of events and the timing of the interim analysis.

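### Censoring at last contact can keep patients without rhythm monitoring at risk and event-free in the Kaplan–Meier curve of the primary endpoint

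*Protocol article*

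**What the plan says.** All references are to the protocol article.

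- **Endpoint (Outcome measurement).** A documented atrial tachyarrhythmia "lasting 30 s following a blanking period of 3 months after CMIV".
- **How it can be documented (Data collection).** "Study visits are scheduled to occur before randomization and at 3, 6, and 12 months", and "48- to 72-h Holter monitoring will be conducted at each visit". Between visits, patients with symptoms "will be encouraged to undergo electrocardiography (ECG) during their symptomatic periods", and extra Holter or event monitoring is offered when an acute episode could not be recorded.
- **Telephone contact (Adverse events monitoring and interim analysis).** Two staff members collect cardiovascular events and other serious adverse events, and "they will follow up specifically for these events by telephone every month for every participant with a phone number", given prior consent. No rhythm recording is described for these calls.
- **Censoring (Statistical analysis).** Prefaced by the qualifier *in general*: "the last date of contact for each patient will be considered the censoring date for those without any primary outcome event".
- **Where the censoring date is used (same section).** "The cumulative incidence of the first occurrence of any event in the primary endpoint will be plotted by the Kaplan–Meier curve".
- **Primary comparison (same section).** The proportions with recurrence "will be compared using the chi-square test". The only stated rule for loss covers patients lost or dead before the 3-month visit.

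**The concern.** A censoring date should mark the end of the time in which an event could have been observed. For an endpoint that needs a rhythm record, that is the last rhythm record. The article uses last contact instead, does not limit contact to a rhythm assessment, and schedules a monthly contact that cannot show the endpoint.

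Take a patient who has the month-3 Holter, declines those at months 6 and 12, and answers the telephone to month 12. Under the rule as written, this patient contributes 12 − 3 = 9 months of event-free time in which a silent recurrence had no chance of being seen. Such patients enlarge the risk set without being able to add silent events, so the curve understates cumulative recurrence. The curve displays the primary endpoint over time, and its height at 12 months is likely to be read as the recurrence rate.

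**Working it through.** **Inputs.** Freedom from recurrence of 0.821 and 0.621 (recurrence 17.9% and 37.9%), two-sided alpha 0.05, power 0.90 and 101 per group come from Sample size estimation. Holters at months 3, 6 and 12 come from Data collection. The article does not tie the two rates to a time point; they are taken here as 12-month cumulative incidences. The share *f* of an arm with no rhythm record after month 3 but telephone contact to month 12 is an assumption, because the article gives no value.

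**Step 1: the plan's own figure.** Unpooled normal approximation:

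n = [0.821 × 0.179 + 0.621 × 0.379] × (1.960 + 1.282)² / 0.200² = 100.43, rounded up to 101.

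This matches. The sample size is not in dispute, and these rates can be used for illustration.

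**Step 2: Kaplan–Meier under last-contact censoring.** Assume a constant hazard from month 3 to month 12, detection at the month-6 and month-12 Holters, and no recurrence detected in the share *f*. With S = 1 − p at month 12, the chance of a first event by month 6 is q6 = 1 − S^(1/3). The chance from month 6 to 12, given none before, is q12 = 1 − S^(2/3).

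Placebo, S = 0.621: q6 = 0.147, q12 = 0.272. With f = 0.10:
- detected at month 6: 0.90 × 0.147 = 0.132
- detected at month 12: 0.90 × (1 − 0.147) × 0.272 = 0.209
- nobody leaves the risk set without an event before month 12, so cumulative incidence = 0.132 + 0.209 = 0.341

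In general the estimate is p × (1 − f), whatever the shape of the hazard:

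| f, both arms | Placebo | Dapagliflozin | Difference (points) |
|---|---|---|---|
| 0% | 37.9% | 17.9% | 20.0 |
| 5% | 36.0% | 17.0% | 19.0 |
| 10% | 34.1% | 16.1% | 18.0 |
| 20% | 30.3% | 14.3% | 16.0 |

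With equal *f* the ratio of the two incidences does not move: 37.9/17.9 = 34.1/16.1 = 2.12.

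**Step 3: Kaplan–Meier under last-rhythm censoring.** The share *f* leaves the risk set at month 3. At month 6 the risk set is (1 − f) and the events are (1 − f) × q6, so the survival factor is 1 − q6; month 12 works the same way. Cumulative incidence is 1 − (1 − q6)(1 − q12) = 1 − S, that is, 37.9% and 17.9% for any *f*. This holds if stopping is unrelated to rhythm.

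**Step 4: credit for symptom-driven recording.** If a share *s* of recurrences in these patients is still caught through symptoms, the last-contact estimate becomes p × [1 − f(1 − s)]. With f = 10% and s assumed to be one half, the factor is 0.95, giving 36.0% and 17.0%. Step 2 is therefore the worst case for each *f*.

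**The case against.** Several points on the other side are sound.

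- **Contact is undefined.** The sentence is qualified by *in general*, the calls are described in another section for another purpose, and the two sections do not refer to each other. That a call counts as a contact is the ordinary reading, not a stated rule. This stands. It does not remove the problem, because nothing in the article excludes calls and two analysts could draw different curves from the same data.
- **The loss is smaller than the worst case.** Symptom-driven ECGs and extra monitoring do not depend on attending the later visits, so mainly silent recurrences are missed. This stands. In addition, f = 10% equals the whole dropout allowance in Sample size estimation.
- **The replacement rule has its own bias.** If patients who feel well are the ones who stop, censoring them early removes low-risk patients and pushes the estimate up. Symptom-triggered ECGs also extend follow-up selectively in symptomatic patients. This stands and belongs among the costs of the change.

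Two stronger readings are tempting. A reader might infer that the primary result is biased or loses power. The article does not support that as a consequence of this rule: the chi-square test compares proportions and uses no censoring date. How patients without later rhythm records enter that test is a separate question, which changing the censoring date would not settle. A reader might also infer a biased comparison between arms. The article names no log-rank test, Cox model or hazard ratio to which such bias would attach, and gives no ground for expecting monitoring to stop more often in one arm.

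**Conclusion.** The point holds for the Kaplan–Meier curve. The stated censoring rule does not match an endpoint that needs a documented rhythm, and followed as written it biases cumulative recurrence downward. The worst case at an assumed f = 10% in both arms is 34.1% vs 16.1% instead of 37.9% vs 17.9%, with the difference falling from 20.0 to 18.0 points. This rests on counting telephone calls as contacts, on treating the design rates as 12-month incidences, on an *f* that the article does not give, and on no recurrence being detected in the patients concerned. The true loss would be smaller to the extent that symptomatic episodes are recorded. The primary chi-square test and the sample size of 101 per group are unaffected. This is a cheap improvement to the time-to-event estimate.

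**What to change.** Replace the censoring sentence with one along these lines: for the arrhythmia endpoint, patients without an event are censored at their last rhythm assessment (end of the last Holter, or the last ECG or event recording); for MACCE only, they are censored at last contact, including by telephone.

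The cost is one sentence and no new data. Follow-up time in the curve becomes slightly shorter and its interval wider. The text should acknowledge that the estimate is unbiased only if stopping monitoring is unrelated to rhythm.

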**Conclusion:**

DETAIL-CMIV will determine whether the sodium-glucose cotransporter-2 inhibitor dapagliflozin, added to guideline-recommended post-operative AF therapies, safely reduces the recurrence rate of AF in patients with and without T2DM or HF.

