### Sample size estimation

According to our published work, the recurrence rate of AF after CMIV is 37.9% in patients without oral dapagliflozin therapy.^14^ A recent study showed that dapagliflozin reduced the recurrence rate of AF by 17.1% after RFCA.^13^ We assume a more progressive effect of 20% relative risk reduction. The two-proportion test power analysis was performed by using PASS 15 software ([name]), and the algorithms were as follows: (i) power calculation method: normal approximation; (ii) alternative hypothesis: two sided; (iii) test type: *Z*-test (unpooled); (iv) power: 0.9; (v) alpha: 0.05; (vi) group allocation: equal (*N*1 = *N*2); (vii) input type: proportions; (viii) P1 (Group 1 proportion|H1): 0.821; and (ix) P2 (Group 2 proportion): 0.621. Therefore, the estimated sample size required to detect a significant difference in the chi-square test between the two groups under the conditions of a significance level of 5% on both sides and a power of 90% is 101 cases per group. Assuming a dropout rate of 10%, the target number of enrolled patients has been set at 120 cases per group for a total of 240 cases for the two groups.

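### The primary treatment comparison is an unadjusted chi-square although prognostic baseline data are already collected: a valid test, but efficiency forgone that a prespecified adjusted model could recover

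*Protocol article*

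**What the plan says.** In the Protocol article, Statistical analysis, the proportions with recurrence in the two arms are compared by chi-square test. The section then adds that "the logistic regression model will be used to assess possible predictors for recurrence at follow-up", with prespecified characteristics tested univariately before a multivariable step. It does not say that treatment is in this model or that the model adjusts the treatment effect.

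Randomization and blinding gives 1:1 allocation in blocks of ten and names no stratification factor.

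Data collection lists "Peri-operative clinical and baseline data, such as the type of AF, medical history, laboratory results, complications, cardiac ultrasound features", together with operative information. T2DM and HF are not named there; they would ordinarily fall under medical history. Left atrial diameter (an exclusion criterion) and stand-alone versus concomitant surgery (part of the inclusion criteria) must be known for every patient.

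The Abstract's Conclusion says the trial will determine whether the drug "safely reduces the recurrence rate of AF in patients with and without T2DM or HF". Objectives speaks of an effect irrespective of those conditions.

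Sample size estimation takes it that "the recurrence rate of AF after CMIV is 37.9% in patients without oral dapagliflozin therapy" and enters "P1 (Group 1 proportion|H1): 0.821; and (ix) P2 (Group 2 proportion): 0.621".

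**The concern.** The population is mixed: stand-alone and concomitant surgery, patients whose catheter ablation failed, any T2DM or HF status, and left atrial diameters up to 65 mm. If some of these features predict recurrence, a comparison that ignores them has a larger standard error than it needs. The plan does use baseline characteristics in a model, but to look for predictors and not to sharpen the estimate the trial exists to produce. Choosing them by univariate screening would also make that model a poor basis for a treatment estimate, because its content would depend on the outcome data.

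At stake is a modest amount of precision, and the credibility of any adjusted result reported later. Covariates fixed before unblinding are convincing; covariates chosen afterwards are not.

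**Working it through.** **Inputs from Sample size estimation.** Control recurrence 0.379 (recurrence-free 0.621); treated recurrence 0.179 (recurrence-free 0.821); two-sided alpha 0.05; power 90%; unpooled Z-test; 10% dropout; 120 enrolled per arm, so 120 × 0.90 = 108 evaluable.

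**Assumed, not in the article.** R², the share of outcome variance explained by the covariates: 0.02 to 0.20. Share of patients with T2DM or HF: 15% to 50%.

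**1. The plan's own figure.** Sum of variances: 0.379 × 0.621 + 0.179 × 0.821 = 0.2354 + 0.1470 = 0.3823. Then n = (1.960 + 1.282)² × 0.3823 / 0.20² = 100.4, so 101 per arm. This agrees with the stated result: "a significance level of 5% on both sides and a power of 90% is 101 cases per group".

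**2. Power of the planned unadjusted comparison at 108 per arm.** Standard error = √(0.3823/108) = 0.0595. Then 0.20/0.0595 − 1.96 = 1.40, which gives power 91.9% (91.2% with the pooled variance). The 90% target is met.

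**3. Power with adjustment.** Multiply the variance by (1 − R²):

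| Assumed R² | Power at 108 per arm | n per arm for 90% |
|---|---|---|
| 0 (unadjusted) | 91.9% | 101 |
| 0.02 | 92.4% | 99 |
| 0.05 | 93.2% | 96 |
| 0.10 | 94.3% | 91 |
| 0.15 | 95.4% | 86 |
| 0.20 | 96.4% | 81 |

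The gain is about 0.5 to 4.5 percentage points.

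**4. Check by simulation.** 6,000 trials per setting, 108 per arm, one normally distributed prognostic score; chi-square versus logistic regression adjusted for the score:

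- R² about 0.05: 91.2% versus 92.1%
- R² about 0.12: 91.7% versus 93.8%
- R² about 0.22: 92.3% versus 95.8%
- Score not prognostic: 92.0% versus 91.7%, so no gain

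**5. How many covariates the data can carry.** Expected events: 108 × 0.379 + 108 × 0.179 = 40.9 + 19.3, about 60. Treatment plus five single-parameter covariates is six terms, or 60/6 = 10 events per term. Two interactions make eight terms, or 60/8 = 7.5.

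**6. Precision by T2DM or HF status.** The 95% half-width for the risk difference in a subgroup holding share s of patients is 1.96 × √(0.3823/(108s)). This is about 30 points at s = 15%, 23 at 25%, 21 at 30% and 17 at 50%. Power to detect a 20-point interaction is about 22% at s = 15%, 34% at 30% and 39% at 50%.

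**The case against.** The strongest reply is that nothing here is an error. A chi-square test after 1:1 randomisation is valid, the trial was sized for that test, and it reaches its target. The benefit of adjustment rests on a prognostic strength the article does not give. All of this stands, and it is why the point is a recommendation about efficiency.

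Four stronger readings are tempting, and the article does not support them.

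- **That the trial is underpowered because the test is crude.** Step 2 shows otherwise at the design effect. A larger gain, from 80% to 82–88% for R² of 0.05 to 0.20, appears only if the 17.1% reduction cited from a catheter-ablation study is read as absolute points and used as the effect. That is not the effect the trial was sized for. The wording "We assume a more progressive effect of 20% relative risk reduction" does conflict with the 20-point absolute difference entered, but that is a separate and much larger problem: with 37.9% falling to 30.3%, power is about 22% unadjusted and 22–26% adjusted, so adjustment does not rescue it.
- **That unstratified allocation endangers the result.** Chance imbalance is already covered by the type I error rate. For a factor with 50% prevalence, the imbalance has SD √(2 × 0.25/120) = 6.5 points. If the factor shifts recurrence by 20 points (assumed), a one-SD imbalance moves the difference by 1.3 points, against a standard error of about 6.
- **That a T2DM or HF subgroup analysis has been omitted.** The Objectives can be read as an overall effect in all comers. The Discussion does raise benefit in patients without either condition as a hypothesis to be tested, which is harder to read that way. But subgroup and interaction analyses commonly sit in a full protocol or SAP, which is not shown, so their absence from the article is no fault.
- **That every covariate is confirmed as collected.** AF type is named; T2DM and HF are inferred from medical history.

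**Conclusion.** The point holds as a low-to-moderate efficiency recommendation. The article fixes an unadjusted primary comparison and spends its only multivariable model on a screened search for predictors, while plausible prognostic data are already in hand. The planned test is valid and has about 92% power on the plan's own inputs. Prespecified adjustment would take this to 92.4–96.4% over an assumed R² of 0.02 to 0.20, and would leave it unchanged if the covariates do not predict recurrence. These figures rest on the 20-point absolute effect, 108 evaluable patients per arm and the assumed R².

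On T2DM and HF, the pooled test supports a statement about the pooled population only. Separate estimates are worth showing but will be too imprecise to carry a conclusion of their own.

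**What to change.** Estimate the primary treatment effect in one prespecified model, for example logistic regression with a standardised risk difference, so that the result stays on the scale used for sizing. Include treatment and a short fixed list: AF type, left atrial diameter, stand-alone versus concomitant surgery, T2DM and HF. Use only variables known before randomisation, which excludes the post-operative complications also being recorded. Do no univariate screening, and fix the list before unblinding. Keep the chi-square as a supportive analysis and the predictor model as exploratory.

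Separately, as a secondary descriptive analysis outside the primary model, report the treatment effect by T2DM and by HF status with 95% confidence intervals. Word the conclusion as the effect in the pooled population.

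Cost: a change of analysis wording, plus confirmation that T2DM and HF are recorded at baseline for every patient. No change to sample size, visits or randomisation is needed. The limits are the roughly 60 expected events, which leave little room beyond this list, and wide subgroup intervals.
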